#### b) Secondary Objectives

In addition to the six secondary objectives listed above for the first analysis, a further objective will characterize all system-related complications between the implant procedure and the four month follow-up visit to confirm that the complication-free rate is greater than 80%. The objective is analyzed using a one-sided exact test with a 95% confidence interval.

The secondary objectives for system-related complications, lead handling, and lead performance are evaluated under the "fixed-sequence method" in order to preserve the overall type one error of these objectives for regulatory purposes. The three objectives are tested sequentially with formal statistical tests. Lead handling is analyzed using a 95% confidence interval to assess whether the differences in overall lead handling characteristics are statistically equivalent between the EnRhythm MRI cohort and the 5076 historical comparison group (Δ = 1.5 units). Lead performance is analyzed using 95% confidence intervals to analyze whether the differences in capture and sensing are statistically equivalent between the EnRhythm MRI cohort and the 5076 historical comparison group (Δ = 0.5 V for capture, 0.9 mV for atrial sensing, and 2.5 mV for ventricular sensing).

#### c) Additional analyses

In addition to the additional analysis listed above for the first analysis, a further analysis will summarize aberrant or undesirable behaviour of the MRI SureScan programming mode, for which information is collected pertaining to its use and performance.

Furthermore, a summary of whether safeguards and procedures were followed at the time of MRI scans will be provided. Information is collected pertaining to whether safeguards and procedures for the preparation, programming, and monitoring around the time of the MRI scans were followed for the cardiology and radiology teams.

### Sample size and data use for analysis

Sample size calculations for both sets of objectives exclude attrition and provide at least 80% power with a type one error rate (alpha) of 0.05 (first set) or 0.025 (second set). No alpha adjustment was necessary for the two analyses, since the objectives are different and both sets will each be analyzed only once. Sample sizes were calculated separately for each primary objective and the largest requirements (62 patients per group for the first set, 122 per group for the second set) were further increased to 156 and 470 total patients, respectively, for consideration of estimated study attrition and added regulatory requirements.

Pre-specified analysis exclusion criteria were listed in the investigational plan and include the following:

• Data from visits outside the 1 month post-MRI visit window are excluded from the primary analyses of capture and sensing objectives, but are included in a secondary sensitivity analysis of these objectives.

• Data from patients whose MRI scans were not performed according to protocol requirements are excluded from the analyses of capture, sensing, MRI-related complications, labeling instructions, occurrence of arrhythmias, and lead impedance.

• Data from patients in atrial arrhythmias at the time of electrical data collection are excluded from analyses of atrial capture and sensing objectives at affected visits.

• Data from patients with unresolved lead dislodgments are excluded from analyses of capture, sensing, and impedance objectives.

• Data from patients with a pacing threshold difference exceeding 0.5 V prior to the MRI visit, which is indicative of an abnormal lead/tissue interface, are excluded from analyses of capture and sensing objectives.

• Pacing capture data lacking required threshold strip documentation or not measured at 0.5 ms are excluded from the analysis of the capture threshold objective.

• Patients unable to capture will be assigned a capture threshold value of 6 V at affected visits for the purpose of calculating descriptive statistics.

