#### b) Secondary Objectives

All secondary objectives and additional analyses are analyzed using descriptive statistics but are not statistically evaluated.

1. Confirm that labelling instructions for completing the MRI scans were followed to ensure patient safety. Occurrence of system-related adverse device effects due to insufficiencies of the labelling or inadequacies of the labelling are used.

2. Characterize occurrence of sustained ventricular arrhythmias and asystole seen during MRI scans.

3. Characterize all implant procedure-, pacing system- and MRI procedure-related complications and observations to four months post-implant.

4. Summarize atrial and ventricular lead impedance up to four months post-implant.

5. Characterize the lead handling of the CapSureFix MRI lead model 5086 MRI in relation to the commercially available model 5076. A seven-point questionnaire is used.

6. Characterize four months pacing threshold and sense amplitude of the MRI group and control group in relation to the commercially available lead Model 5076.

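### As written, the exclusions for unstable thresholds and unresolved dislodgments also reach the formal comparison with the historical 5076 lead, where those events are outcomes of the lead under test

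*Protocol article*

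**What the plan says.** The list of analysis exclusions (Protocol article, Sample size and data use for analysis) contains two rules that matter here.

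- Stability: "Data from patients with a pacing threshold difference exceeding 0.5 V prior to the MRI visit, which is indicative of an abnormal lead/tissue interface". The reach of this rule is stated without a limit: such data "are excluded from analyses of capture and sensing objectives".
- Dislodgment: "Data from patients with unresolved lead dislodgments are excluded from analyses of capture, sensing, and impedance objectives".

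A third item in the list concerns loss of capture: "Patients unable to capture will be assigned a capture threshold value of 6 V at affected visits for the purpose of calculating descriptive statistics". It assigns a value and does not exclude the patient.

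The secondary objectives of the second analysis make lead performance a formal test of whether "differences in capture and sensing are statistically equivalent between the EnRhythm MRI cohort and the 5076 historical comparison group", using 95% confidence intervals and margins of "Δ = 0.5 V for capture, 0.9 mV for atrial sensing, and 2.5 mV for ventricular sensing". It is one of three objectives tested in a fixed sequence to control type I error. The time point comes from the matching secondary objective of the first analysis, which the second analysis carries over: "Characterize four months pacing threshold and sense amplitude of the MRI group and control group in relation to the commercially available lead Model 5076".

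**The concern.** The two exclusions suit the MRI question. A stability check made before the scan falls on both randomised arms and does not by itself favour either, and a lead known to be displaced says little about heating by the scan.

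The 5076 comparison asks something else: whether the modified lead paces and senses as well as the lead it derives from. There is no randomisation, and every event after implantation belongs to the lead being assessed. An unstable threshold in the first weeks, or a dislodgment that is never resolved, is part of the answer. Removing patients on those grounds conditions the test on the lead having behaved well. At stake is a formal equivalence claim that the article says serves regulatory purposes.

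**Working it through.** **Scope.** Neither rule contains words limiting it to primary or randomised objectives. The list as a whole clearly goes beyond the primary objectives: it names impedance, labelling instructions and arrhythmias, which appear only among the secondary objectives. Lead performance is defined in terms of capture and sensing. On the literal reading, both rules apply to it.

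**Transfer to the historical group.** The stability rule is timed by the MRI visit. The article gives no such visit, or an equivalent time after implantation, for the 5076 group, and does not say which exclusions its data underwent. The only sensitivity analysis stated in the list concerns visits outside the time window.

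**The plan's own figures.** No sample size, standard deviation or exclusion rate is given for the 5076 comparison, so there is no plan figure to reproduce for it. The 122 per group of the second set does reproduce: Farrington-Manning with both proportions 93%, margin 10%, one-sided alpha 0.025 and power 80% gives 121.5, rounded up to 122. This point does not affect it.

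**Size of the shift.** Let retained patients have mean threshold m, and let a share f be excluded with mean m + e.

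- Mean of all patients: (1 − f)·m + f·(m + e) = m + f·e.
- Mean of retained patients: m.
- Understatement of that cohort's mean: f·e.
- If the historical data are also filtered, the shift in the difference (new minus historical) is f_new·e_new − f_hist·e_hist. It cancels only when the two products are equal. A lead that is unstable more often would still have part of its deficit hidden.

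Neither f nor e is in the document. The table shows f·e for assumed values with one cohort filtered, and in brackets its share of the 0.5 V capture margin.

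| f | e = 0.5 V | e = 1 V | e = 2 V | e = 5 V |
|---|---|---|---|---|
| 1% | 0.005 V (1%) | 0.01 V (2%) | 0.02 V (4%) | 0.05 V (10%) |
| 2% | 0.01 V (2%) | 0.02 V (4%) | 0.04 V (8%) | 0.10 V (20%) |
| 5% | 0.025 V (5%) | 0.05 V (10%) | 0.10 V (20%) | 0.25 V (50%) |
| 10% | 0.05 V (10%) | 0.10 V (20%) | 0.20 V (40%) | 0.50 V (100%) |

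The 5 V column stands for excluded leads close to the 6 V non-capture value.

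**Direction.** With e above zero, the new lead's mean threshold is understated. If the new lead is truly worse, this moves the difference toward zero and so toward equivalence. Dropping extreme values would also tend to narrow the interval. If e is near zero or negative, there is no such gain.

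**The case against.** The strongest reply is that the article's labels point to a narrower scope. The 5076 comparison has its own name, lead performance. The exclusion for scans not done to protocol lists several primary and secondary objectives but none of the three in the fixed sequence. The item on missing strip documentation speaks of a single capture objective. The dislodgment rule adds impedance by name but not lead performance. On this reading the exclusions already stop at the MRI-related objectives. That is plausible, but no sentence says so, and the secondary objective uses the same words, capture and sensing, that define the exclusions' scope.

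The reply is stronger against firmer versions of the point:

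- A reader might infer that poor performers leave the new-lead cohort only and that the 5076 leads are unselected. The article is silent on how the 5076 data were filtered, and the list is an extract from an investigational plan that is not shown.
- A reader might infer a definite loss of margin, for example 3% to 10% excluded at 1 V plus 2% at 5 V: 0.13 to 0.20 V, or 26% to 40% of 0.5 V. All of these inputs are assumed. Part of the sum treats non-capture as an exclusion, which it is not, and one patient could meet both rules.
- A reader might take every excluded patient for a poor performer. A difference above 0.5 V may also be a fall, and only unresolved dislodgments are removed.
- A reader might think that lead failures disappear from view. Neither rule names the system-related complication objective, so dislodgments that meet the complication definition still count there, in the same fixed sequence.

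**Conclusion.** The point holds in a limited form. Read literally, both exclusions extend to a formally tested, non-randomised comparison in which the excluded events are outcomes of the new lead. No counterpart of the stability rule is stated for the 5076 group, and no analysis without these exclusions is stated. The result may be biased toward equivalence, provided that excluded patients have higher four-month thresholds. The rule's own rationale makes this likely, but the document does not show it.

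The size is undetermined. Excluding 5% with an excess of 1 to 2 V would give 0.05 to 0.10 V, 10% to 20% of the capture margin, and the assumed grid as a whole runs from 1% to 100%. For sensing, not even an illustrative amplitude deficit can be drawn from the document. The criticism does not extend to the randomised primary comparisons or to the sample size of 122 per group.

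**What to change.** State that both exclusions apply only to the randomised MRI-versus-control objectives, and analyse lead performance against the 5076 group on all implanted patients with a four-month measurement. Alternatively, apply one identical rule at the same time after implantation in both cohorts, and add an analysis without the exclusions.

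In either case, report how many patients each rule excludes. Handle non-capture in a sensitivity analysis: the 6 V value is stated for descriptive statistics only, and in a formal comparison of means an assigned value could drive both the mean and the spread.

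The cost is a sentence or two in the plan and one additional analysis. The lead-performance estimate may become slightly less favourable and more variable.

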### Independent advisory committees

The Investigator will be asked to assess the relationship of each adverse event to the pacing system, implant procedure and/or the MRI scan. An Adverse Event Advisory Committee (AEAC) will review the classifications of all adverse device effects, deaths, technical observations and adverse events at regular intervals.

A Scan Advisory Committee developed similar MRI scan protocols for the different MRI machines from the three manufacturers and assisted in the validation of the individual MRI scans. Furthermore, this committee will regularly review the performed MRI scans and determine if the scan data acquired will be included in the analysis.

The trial is supervised by an independent data monitoring committee (DMC), consisting of one statistician, one radiologist and one cardiologist, to review safety data as well as to review periodically the efficacy data.

### Ethical aspects

The study will be conducted according to the investigational plan, the Declaration of Helsinki concerning medical research and in accordance with local laws and regulations of countries where patients are enrolled. Each center needs Institutional Review Board/Medical Ethics Committee approval of the study protocol and written patient informed consent prior to enrolment. Patients may withdraw from the study at any time without giving reasons and without jeopardizing their further treatment. The investigator may also withdraw patients if this is in their best interests.

## Discussion

This study has been designed to confirm the safety and efficacy of a new pacing system in the MRI environment.

There is much published work on the effects of MRI scans on patients with implanted devices and recommendations for minimizing these hazards [4-6,8-15]. The inference of these reports indicates that dedicated pacing systems are needed to avoid complications including arrhythmias, inhibition of pacing output and triggered stimulations, and RF-related heating of the pacing leads with potential thermal damage at the electrode/tissue interface, although there remains some controversy over this need [3]. Systems designed for safe use in the MR environment must be considered in the light of a rapidly increasing number of MR studies being performed worldwide in all types of patient. Implanted device patients at present are clearly clinically disadvantaged by being unable safely to undergo MRI in many conditions that they may develop.

A new system has been designed to address the safety issues of MRI scanning in patients with implanted devices. This requires careful clinical assessment, which is the object of this trial using a randomization technique to those who will be scanned and a control group who will not.

In the future, it is hoped, assuming this trial to be successful, that MRI-compatibility may be extended to more complex devices such as those that deliver cardiac resynchronization therapy and implantable cardioverter defibrillators.

## Abbreviations

ACC: American College of Cardiology; AHA: American Heart Association; AE: Adverse Event; AEAC: Adverse Event Advisory Committee; C1: Cervical Vertebra 1; DMC: Data Monitoring Committee; HRS: Heart Rhythm Society; ICD: Implantable Cardioverter Defibrillator; IPG: Implantable Pulse Generator; MR: Magnetic Resonance; MRI: Magnetic Resonance Imaging; T12: Thoracic Vertebra 12; US: United States; SAR: Specific Absorption Rate.
